## Abstract

**Background:**

Transcranial direct current stimulation (tDCS) is a promising new technique to optimize the effect of regular Speech and Language Therapy (SLT) in the context of aphasia rehabilitation. The present study focuses on the effect of tDCS provided during SLT in the sub-acute stage after stroke. The primary aim is to evaluate the potential effect of tDCS on language functioning, specifically on word-finding, as well as generalization effects to verbal communication. The secondary aim is to evaluate its effect on social participation and quality of life, and its cost-effectiveness.

**Methods:**

We strive to include 58 stroke patients with aphasia, enrolled in an inpatient or outpatient stroke rehabilitation program, in a multicenter, double-blind, randomized controlled trial with two parallel groups and 6 months’ follow-up. Patients will participate in two separate intervention weeks, with a pause of 2 weeks in between, in the context of their regular aphasia rehabilitation program. The two intervention weeks comprise daily 45-minute sessions of word-finding therapy, combined with either anodal tDCS over the left inferior frontal gyrus (1 mA, 20 minutes; experimental condition) or sham-tDCS over the same region (control condition). The primary outcome measure is word-finding. Secondary outcome measures are verbal communication, social participation, quality of life, and cost-effectiveness of the intervention.

**Discussion:**

Our results will contribute to the discussion on whether tDCS should be implemented in regular aphasia rehabilitation programs for the sub-acute post-stroke population in terms of (cost-)effectiveness.

**Trial registration:**

Nederlands Trail Register: NTR4364. Registered on 21 February 2014.

**Electronic supplementary material:**

The online version of this article (doi:10.1186/s13063-016-1505-z) contains supplementary material, which is available to authorized users.

## Background

Aphasia is present in about 30 % of patients immediately after stroke [1]. In the first weeks and months, considerable recovery may occur; however, about 20 % are left with chronic deficits at 6 months post stroke [2, 3]. There is increasing support for the efficacy of Speech and Language Therapy (SLT) in order to diminish the language and communication deficits that people with aphasia encounter [4]; however, it remains a challenge to optimize the effect of aphasia therapy.

Transcranial direct current stimulation (tDCS) is a promising new technique to optimize the effect of regular SLT in the context of aphasia rehabilitation [5]. It is safe and easy to apply and has limited side effects [6]. tDCS modulates cortical excitability by delivering weak electric currents to the cortex via two electrodes applied to the skull [7]. The effect of tDCS depends on the polarity of the electrodes: anodal tDCS enhances neuronal excitability while cathodal tDCS diminishes neuronal excitability. This effect is related to a change in the resting membrane potential. Anodal tDCS leads to de-polarization, increasing the chance for an action potential, and cathodal tDCS leads to hyper-polarization [8, 9]. tDCS is also related to neuroplasticity. Specifically, processes like long-term potentiation and secretion of brain-derived neurotrophic factor (BDNF) are associated with tDCS application [10]. The potential benefits of tDCS applied during SLT have been described since 2008 [5, 11–17]. However, these studies have some methodological limitations such as small sample size and lack of randomization.

The application of tDCS to enhance the effect of SLT is associated with the notion that tDCS may have a role in rebalancing the activity of both hemispheres post stroke. Language processing is strongly lateralized to the left hemisphere (LH), at least in right-handed healthy individuals [18–21]. After LH damage and aphasia, the right hemisphere (RH), may show increased activity. Whether this increased activity in the RH is adaptive or maladaptive, is an unresolved issue [22–24]. However, most studies indicate that, in the long term, LH perilesional recruitment is associated with better aphasia recovery, while RH recruitment is related to incomplete recovery [25–27]. In line with these observations, most studies use tDCS as a tool to promote LH perilesional recruitment.

Across studies, different electrode configurations are used to promote LH perilesional recruitment. In some studies anodal tDCS [13, 15, 16] is applied either to the left inferior frontal gyrus (IFG: Broca’s area) or to the left superior temporal gyrus (Wernicke’s area), while other studies use cathodal tDCS to inhibit the RH homolog areas, so as to disinhibit the LH [14, 28]. Few studies use an individual approach for electrode configurations [11, 29]. Anodal tDCS to the left IFG, with the cathode placed on the contralateral supra-orbital region, is the most common configuration, which has been supported by studies investigating this further with functional magnetic resonance imaging (fMRI) [30, 31] and computer modeling [32]. Predominantly, tDCS studies choose word-finding therapy as the behavioral treatment component. Irrespective of electrode configurations, studies point to an additional effect of tDCS on language functioning, when combined with SLT [5, 11–17, 29].

Studies evaluating tDCS in sub-acute aphasia rehabilitation are limited [26]. Evaluating the potential of tDCS in patients with sub-acute aphasia is important, as the larger proportion of language treatment for stroke patients is provided in the sub-acute phase, during the first weeks and months post stroke. During these first months, the recovery rate is highest [33].

Therefore, the aim of the present study is to investigate the effect of tDCS in sub-acute stroke patients with aphasia who are enrolled in regular stroke rehabilitation services. In line with studies applying tDCS in the chronic stage, we use the most common electrode configuration, i.e., anodal tDCS over the left IFG as compared to sham-tDCS, in combination with disorder-oriented aphasia therapy, aimed at word-finding. The cathode is placed on the contralateral supra-orbital region.

### Objective

The present study focuses on the effect of tDCS provided during SLT in the sub-acute stage after stroke. The primary aim is to evaluate the effect of tDCS on language functioning. The primary outcome measure is word-finding. Secondary outcome measures are verbal communication, social participation, quality of life, and the cost-effectiveness of the intervention.

## Methods

### Study design and procedure

The study is a multicenter, double-blind, randomized controlled trial with two parallel groups and 6-month follow-up. Patients will participate in two separate intervention weeks, with a pause of 2 weeks in between, in the context of regular aphasia rehabilitation (see Fig. 1). During each intervention week, regular SLT sessions are replaced by daily 45-minute sessions of word-finding therapy, combined with either anodal tDCS over the left IFG (1 mA, 20 minutes; experimental condition) or sham-tDCS over the same region (control condition). The cathode is placed on the contralateral supra-orbital region. To our knowledge, a parallel design with two separate intervention weeks has not been used before in the tDCS literature. This design allows measurements before and after each intervention week, thus providing information on the recovery pattern over time within one subject.

**Fig. 1 Fig1:**
[figure not shown]
Study design with two separate intervention weeks

All other therapies in the participant’s stroke rehabilitation program, such as physical therapy or occupational therapy remain unchanged and are offered following the stroke rehabilitation protocol of each participating rehabilitation center.

### Setting and study population

Stroke patients with aphasia, who are receiving regular aphasia therapy, will be screened for eligibility and start the intervention between 3 weeks and 3 months after their stroke. These patients are enrolled in regular stroke rehabilitation (inpatient and outpatient services) in four rehabilitation centers in the Netherlands: Rijndam Rehabilitation (Rotterdam), Libra Rehabilitation (Tilburg and Eindhoven), Revant Rehabilitation (Breda) and De Hoogstraat Rehabilitation (Utrecht). Table 1 lists the inclusion and exclusion criteria. We strive to include 58 patients, based on a power analysis (see section Data analysis). Before inclusion, all participants need to sign the informed consent form. Patient information is provided orally as well as in written form, with extra versions in an aphasia-friendly format. This study has been approved by the Medical Ethics Committee (MEC) of the Erasmus MC, University Medical Center Rotterdam. The researcher will report serious adverse events (SAE) to the MEC and SAEs are handled according to the WMO (“Wet Medisch-wetenschappelijk Onderzoek”), the Dutch law for medical scientific research. tDCS is known to be a safe intervention with minimal side effects [6]. Participants who develop post-stroke epileptic seizures before the end of the 4-week intervention will be withdrawn from the intervention, but not from the study; all assessments will be completed (intention-to-treat analysis).

**Table 1 Tab1:** Inclusion and exclusion criteria

Inclusion criteria
1. Aphasia after stroke
2. Less than 3 months post onset
3. Age 18–80 years
4. Near-native speaker of Dutch
5. Being right-handed
6. Able to participate in intensive therapy
Exclusion criteria
1. Subarachnoid hemorrhage
2. Prior stroke resulting in aphasia
3. Brain surgery in the past
4. Epileptic activity in the past 12 months
5. Premorbid (suspected) dementia
6. Premorbid psychiatric disease affecting communication (for example, personality disorder)
7. Excessive use of alcohol or drugs
8. Presence of a cardiac pacemaker
9. Severe non-linguistic cognitive disturbances impeding language therapy
10. Global aphasia, defined as Shortened Token Test score <9 [50] and score 0 on the Aphasia Severity Rating Scale [41]
11. Severe Wernicke’s aphasia, defined as Shortened Token Test score <9 and score 0–1 on the Aphasia Severity Rating Scale
12. Residual aphasia, defined as Shortened Token Test score >28 and score 4–5 on the Aphasia Severity Rating Scale and Boston Naming Test score >150 [40]

### Intervention

In each intervention week, regular SLT sessions are replaced by daily 45-minute sessions of word-finding therapy, combined with either anodal tDCS over the left IFG (1 mA, 20 minutes; experimental condition) or sham-tDCS over the same region (control condition). Therapy is provided by speech and language therapists of the participating centers. The cathode is placed on the contralateral supra-orbital region. The intensity of 1 mA tDCS for 20 minutes and the frequency of five sessions per week is in line with most studies applying tDCS in the chronic stage [11, 13–16]. tDCS is combined with word-finding therapy, because most people with aphasia have word-finding difficulties [34]. The word-finding therapy protocol is based on Cueing Hierarchy Therapy [35]. The participant’s task is to name a picture and, based on the protocol, the therapist uses cueing techniques to help the participant to retrieve and produce the target word correctly. The cue of low stimulus power is presented first, followed by increasingly powerful cues until the correct word is retrieved and produced. Basically, the following cueing hierarchy is used: (1) “What is this?”(e.g., show picture of a tree), (2) “Can you write the word down?”, (3) graphemic cueing (e.g., provide the number of letters), (4) phonological cueing (e.g., provide the first sound, /t/), (5) semantic associations (e.g., “can you tell where you can find these”), (6) therapist says the word (e.g., “tree”), (7) repetition of the target word.

As the relative power of the cues differs across participants with aphasia, the exact cueing hierarchy is personalized. For each picture, even if the picture is named without cues, the participant is encouraged to write or copy the correct word form or, in case of inability to write, to perform an anagram task. The rationale for incorporating production of the written word, is the evidence that activating the written word has a beneficial effect on retrieving spoken words [36].

To ensure relevance of the training material for each participant, stimuli are selected on the basis of individual naming performance at baseline using the European Data Bank (EDB) for oral picture naming [37]. The first 68 items the participant is unable to name correctly within 20 s are selected. These items are divided in two sets of 34 items, matched for word length and word frequency: a therapy set, trained during the word-finding therapy, and a control set, to evaluate generalization effects to untrained items. In the first session 10 items are trained. Then, during each session new items are added, with eight new items in the second session; six new items in the third and fourth session, and four new items in the final session. For the second intervention week a new training set is selected in the same way.

### tDCS

The DC Stimulator PLUS (produced by Eldith), certified as a medical device, class IIa, by the European Union Notified Body 0118 (CE 118), is used in the authorized form. Two electrodes (5 x 7 cm) are placed on the head and fixed with elastic tape; electrode placement is guided by the international 10-10 electroencephalogram (EEG) system and previous studies [15, 38, 39]. The anode is placed on the left IFG, localized as F5, and the cathode is placed on the contralateral supra-orbital region, localized as Fp2. Participants in the experimental condition receive active stimuli of 1 mA during 20 minutes. The stimulation is automatically activated with a fade in of 15 s and after 20 minutes the stimulation is automatically deactivated, with a fade out of 15 s. Participants in the control condition receive inactive stimulation (sham-tDCS), i.e., at first the stimulation is automatically activated with a fade in of 15 s, and then the stimulation is deactivated after 30 s, with a fade out of 15 s. Both the patient and the therapist are blinded for stimulation condition. The electrodes are not removed until completion of the 45-minute therapy session.

### Measurement instruments

Table 2 gives an overview of the measurement instruments being used. The primary outcome measure is the score on the Boston Naming Test (BNT) [40], to assess picture-naming. Secondary outcome measures are chosen to evaluate generalization of treatment effects to verbal communication: the Aphasia Severity Rating Scale (ASRS) [41] to assess spontaneous speech and the Amsterdam Nijmegen Everyday Language Test (ANELT) [42] as a measure for verbal communication in everyday life. Other secondary outcome measures are chosen to evaluate quality of life (EuroQol-5D, [43]; Stroke and Aphasia Quality Of Life questionnaire (SAQOL), [44, 45]), social participation (Community Integration Questionnaire, [46]), and cost-effectiveness (Cost Analysis Questionnaire, [47–49]).

**Table 2 Tab2:** Measurement instruments

Language and communication tests
Boston Naming Test (BNT) [40]
Aphasia Severity Rating Scale (ASRS) [41]
Amsterdam Nijmegen Everyday Language Test (ANELT) [42]
Shortened Token Test [50]
Quality of life questionnaires
EuroQol-5D (EQ-5D) [43]
Stroke and Aphasia Quality Of Life questionnaire (SAQOL) [44, 45]
Other tests
Community Integration Questionnaire (CIQ) [46]
Cost Analysis Questionnaire [47–49]
Barthel Index [51]
Edinburgh Handedness Inventory
Wong-Baker Faces pain rating scale [52]

The primary outcome measure, BNT, is assessed before and after each intervention week (T1, T2, T3, T4) and at 6 months’ follow-up (T5); see Fig. 2. The secondary outcome measures are assessed before the first intervention week and after the second intervention week (T1, T4) and at 6 months (T5). The EuroQol-5D (EQ-5D) and the Cost Analysis Questionnaire are used to evaluate cost-effectiveness during the 4-week intervention period and during the follow-up period.

**Fig. 2 Fig2:**
[figure not shown]
Measurement instruments and test moments

Baseline assessments (T1) include handedness (Edinburgh Handedness Inventory), aphasia severity (Shortened Token Test) [50] and overall functioning (Barthel Index) [51]. To register potential adverse effects, participants are asked to rate their discomfort immediately after each therapy session on the Wong-Baker Faces pain rating scale, a visual analog scale designed for patients with limited verbal skills [52].

To summarize the present study protocol, please see Additional file 1 for an overview of enrollment, intervention and measurement instruments, and see Additional file 2 for an overview of the Standard Protocol Items: Recommendations for Interventional Trials (SPIRIT) checklist.

### Sample size

The power calculation is based on the results of a randomized controlled trial by Baker et al. [11] including stroke patients in the chronic phase. In this study the group of aphasia patients trained with tDCS improved 2.1 points more than a sham-control group on a picture-naming test. Cohen’s *d* effect size was 0.22, which is equal to a Cohen’s *f* of 0.11. For the present study we calculated that, using a study design with two groups and four repeated measurements, a within-patient correlation of 0.75, an alpha of 0.05, a power of 0.80 and a Cohen’s *f* effect size of 0.11, we need a total group of 58 patients (29 patients in each treatment arm).

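### 80% power with 58 patients does not follow from d = 0.22: f = d/2 is not a group-by-time interaction effect, and power on that test is about 14–25% if the total difference is 0.22 SD

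*Protocol article*

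**What the plan says.** The Sample size section takes its effect from a randomised trial in chronic stroke, where the tDCS group "improved 2.1 points more than a sham-control group on a picture-naming test". It reports that the Cohen's d "effect size was 0.22, which is equal to a" Cohen's f of 0.11. That f goes into a calculation "using a study design with two groups and four repeated measurements, a within-patient correlation of 0.75, an alpha of 0.05, a power of 0.80", and the conclusion is that "we need a total group of 58 patients (29 patients in each treatment arm"). The section does not name the test behind the calculation.

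Three other sections bear on it:

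- Setting and study population rests recruitment on this figure: "We strive to include 58 patients, based on a power analysis".
- Measurement instruments places the Boston Naming Test before and after each intervention week (T1 to T4) and at six months (T5). T1 therefore precedes any treatment.
- Data analysis plans a repeated-measurements model with time, group and their interaction.

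**The concern.** The relation f = d/2 is correct for two groups whose means differ by a constant d. A repeated-measures interaction test asks something else, namely whether the group difference changes over occasions. Its f is the spread of the group difference around its own average over time. A constant difference of 0.22 SD has an interaction f of zero. A difference that starts at zero, as randomisation implies at T1, and grows to 0.22 SD has an interaction f well below 0.11.

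If f = 0.11 was entered into an interaction calculation, the 58 patients are powered for a clearly larger effect than the one cited. The article would then tell its readers that the trial has an 80% chance of detecting a difference that it would in fact usually miss.

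**Working it through.** **Inputs** (Sample size section): d = 0.22, f = 0.11, k = 2 groups, m = 4 occasions, ρ = 0.75, α = 0.05, power 0.80, N = 58. From Measurement instruments: T1 is pre-treatment. Assumptions made here: compound symmetry, d in units of the single-occasion SD, arms equal in expectation at T1, no missing data.

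**Step 1. Reproduce 58.** For the interaction, λ = f²·N·m/(1 − ρ), with df (k − 1)(m − 1) and (N − k)(m − 1).

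- λ = 0.0121 × 58 × 4 / 0.25 = 11.23, df 3 and 168, power **0.803**.
- N = 56 gives 0.787, so 58 is the smallest even total that reaches 80%.

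Other readings of the same inputs do not return 58:

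- Group main effect: λ = f²·N·m/(1 + (m − 1)ρ) = 2.807/3.25 = 0.86. Power is 15.0%, and 80% needs N = 530.
- Interaction with 2, 3 or 5 occasions: N = 84, 68 or 52.
- Simple two-sample t test at d = 0.22: 325 per arm.

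The step from f = 0.11 to 58 is therefore arithmetically right for the interaction test. The question is whether 0.11 is the right f.

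**Step 2. The interaction f implied by d = 0.22.** Let d_j be the group difference at occasion j in SD units and d̄ its mean over the four occasions. Then

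f = ½·√[mean of (d_j − d̄)²] and λ = (N/4)·Σ(d_j − d̄)²/(1 − ρ).

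f = 0.11 requires the group difference to vary around its mean with a root mean square of 0.22, for example −0.22, +0.22, −0.22, +0.22. If every d_j lies between 0 and 0.22, that root mean square is at most 0.11, so f is at most 0.055. If the difference starts at 0 and reaches 0.22, the smallest value comes from 0, 0.11, 0.11, 0.22: Σ = 2 × 0.11² = 0.0242 and f = ½·√(0.0242/4) = 0.039.

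**Step 3. Power at N = 58** (λ from the formula above, df 3 and 168):

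| Group difference at T1–T4 | f | λ | Power | N for 80% | Final difference detectable with 80% power at N = 58 |
|---|---|---|---|---|---|
| 0, d/2, d/2, d | 0.039 | 1.40 | 14.3% | 452 | 0.62 SD |
| linear rise to d | 0.041 | 1.56 | 15.5% | 408 | 0.59 SD |
| 0, d, d, d or 0, 0, 0, d | 0.048 | 2.11 | 19.7% | 302 | 0.51 SD |
| 0, 0, d, d | 0.055 | 2.81 | 25.3% | 228 | 0.44 SD |

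**Step 4. More efficient one-df contrasts**, same inputs, two-sample noncentral t with 29 per arm:

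- Change T1 to T4, variance 2(1 − ρ) = 0.50: 21.4%.
- Baseline-adjusted T4, variance 1 − ρ² = 0.4375: 23.8%. The detectable difference at 80% power is about 0.50 SD.
- Linear trend, with a linear rise to d: 23.3%.
- Mean of T2–T4 minus T1, variance (1 − ρ)(1 + 1/3) = 0.333: 29.7%.
- Baseline-adjusted mean of T2–T4, variance (1 + 2ρ)/3 − ρ² = 0.271: 35.3%.

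The last two assume that the full 0.22 SD is present at all three post-baseline occasions.

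**Step 5. A full 0.22 SD gained in each week** (0, 0.22, 0.22, 0.44): Σ = 2 × 0.22² = 0.0968, f = 0.078, λ = 14.5 × 0.0968/0.25 = 5.61, power about 48%.

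**The case against.** The best reply is that the article fixes neither the test nor the time course. Sample size names no F test. Data analysis does not say that time is categorical, that the interaction has three degrees of freedom, or which term is decisive. A full analysis plan may settle this. The trial also gives two intervention weeks, and the article does not say how much treatment produced the cited d.

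Much of this stands, and it limits how the result may be put. A reader might infer that the trial's power simply is 14–25%. The article does not support so flat a statement. That range belongs to the interaction test with a total effect of 0.22 SD. Contrasts on the mean of T2–T4 reach 30–35%, and a gain of 0.22 SD per week gives about 48% on the interaction test and about 70% on baseline-adjusted T4. None of this rescues the stated 80%. If the group main effect was meant, 58 is further off, at 15% power.

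Four further inferences are tempting but not supported:

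- *That d was standardised on the SD of change, so that the gain from the correlation is counted twice.* The text gives 2.1 points and d = 0.22, hence an SD of about 9.5, without saying which SD this is.
- *That a null result would be taken as evidence against tDCS.* The article nowhere says so. The Discussion makes implementation depend on a positive finding, limited adverse effects and cost-effectiveness.
- *That the absence of a dropout allowance adds materially to the problem.* Any loss rate would be the reviewer's own assumption. The article keeps patients withdrawn for seizures under assessment and plans an analysis that tolerates data missing at random.
- *That the planned analysis is invalid.* The error lies in the stated power, not in the model.

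**Conclusion.** The point holds as a misstatement of power. The 58 patients follow correctly from f = 0.11 on an interaction test, but f = 0.11 is two to almost three times the interaction effect that a total difference of 0.22 SD can produce when the arms start equal (0.11/0.055 = 2.0; 0.11/0.039 = 2.8). On that test the chance of detecting the cited effect is about 14–25%, so the trial would miss it in roughly 75–86% of repetitions. No reading tried with equal baselines, a total effect of 0.22 SD and ρ = 0.75 exceeds about 35%.

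This rests on one inference, that the interaction formula was used, which is well supported because it alone returns 58 and it matches the planned model. It also rests on compound symmetry, d in single-occasion SD units and complete data. The figure should be corrected because recruitment is justified by it and the correction is cheap.

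**What to change.** Keep N = 58. Remove the statement that 80% power follows from d = 0.22, and restate the figure for the interaction test, for example:

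> Under compound symmetry with ρ = 0.75, 58 patients give 80% power on the group-by-time interaction (T1–T4) for a post-treatment difference of about 0.44–0.62 SD, depending on the time profile. Power for a total difference of 0.22 SD is about 14–25%.

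Name the test on which the calculation rests. If a one-df contrast is the intended primary test, state that contrast and give its own power instead. For baseline-adjusted T4 this would be about 24% at 0.22 SD and 80% at about 0.5 SD. Those numbers should not be quoted unless that analysis is actually specified, since Data analysis does not currently describe it.

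The cost is a reworded paragraph and a less favourable figure. No patients are added, which matters because Trial status reports 44 already included.
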